### Baseline, disease and treatment-related data

In addition to the outcome variables mentioned above, the following data will be collected:

***Intrinsic variables (baseline data)***:AgeGenderWeightHeightComorbidity

***Disease-related variables at admission***:Reason of admission to the ICU (*i.e.*, type of disease or injury and type of intervention)Serum lactate concentration at baseline (sodium fluoride tube)IAP level at baselineUrinary creatinine level at baseline (sediment tube)Acute Physiology and Chronic Health Evaluation II (APACHE II) score at baseline; this is a validated and commonly applied severity of disease classification system [24]. An integer score ranging from 0 to 71 is computed based upon 12 routine physiological measurements with a higher scores implying a more severe disease and a higher risk of death.Acute Physiology and Chronic Health Evaluation IV (APACHE IV) score at baseline; this standardized scoring metrics was developed in 2005 as an improved version of the APACHE II. The previously used set of equations were re-evaluated and improved where needed. The most important change involved the new categorization of disease groups [25].Simplified Acute Physiology Score II (SAPS II) at baseline; this score was designed to measure the severity of disease for patients admitted to Intensive care units aged 15 or more [26]. The SAPS II score is calculated from 12 routine physiological measurements during the first 24 hours of ICU admission, information about previous health status and some information obtained at admission. The computed score has a range from 0 to 163 points and a predicted mortality between 0% and 100%. Higher scores imply a more severe disease and a higher risk of death.Sequential Organ Failure Assessment (SOFA) score at baseline; this score is a validated and commonly used score to track a patient’s status during the stay in an ICU. The SOFA score is a scoring system to determine the extent of a person’s organ function or rate of failure [27-31]. The score is based upon six different scores, one each for the respiratory system (*i.e.*, PaO2/FiO2 ratio), the cardiovascular system (*i.e.*, mean arterial pressure and vasopressor requirement), the hepatic system (*i.e.*, bilirubin level), the coagulation system (*i.e.*, platelet count), the renal system (*i.e.*, creatinine level or urine output), and the neurological system (*i.e.*, Glasgow Coma Score). For each of these systems, a maximum of four points can be attributed. SOFA scores are determined on a daily basis during ICU admission.

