The prognostic role of the I-FABP and Claudin-3 on development of IAH, ACS, (increasing) organ dysfunction (based upon SOFA increase) or mortality will be assessed. This analysis will be performed with Stata software, version 10.0 or higher (StatCorp LP, College Station, TX, USA), using the generalized linear latent and mixed model (GLLAMM) framework. Herein, the binary outcome IAH (or new organ dysfuncion or ACS or mortality) will be used as dependent variable, and the level of I-FABP or Claudin-3 will be included in the model as time-dependent variable. Patient ID will be included as clustering variable as up to 13 measurements per patient will be available. Additional covariates such as age, gender, number of IAH risk factors, and BM will be entered into the model in order to evaluate their effect on the relation between biomarker level and outcome. Random intercept and slope will be considered. Results will be expressed as Odds Ratios with their corresponding 95% confidence interval and p-values.

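### The prognostic model names no baseline severity covariate, so an I-FABP odds ratio for mortality may only restate severity at entry, and the one for SOFA increase may be distorted

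*Protocol article*

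**What the plan says.** The Statistical analysis section of the protocol article states that the prognostic role of I-FABP and Claudin-3 for "development of IAH, ACS, (increasing) organ dysfunction (based upon SOFA increase) or mortality will be assessed". Each binary outcome is the dependent variable in a generalized linear latent and mixed model, and "the level of I-FABP or Claudin-3 will be included in the model as time-dependent variable". On clustering it says "Patient ID will be included as clustering variable as up to 13 measurements per patient will be available", and on random effects "Random intercept and slope will be considered". On adjustment it says "Additional covariates such as age, gender, number of IAH risk factors, and BM will be entered into the model", the aim being to see how these covariates affect the relation between marker and outcome. BM is presumably body mass index.

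The section on baseline, disease and treatment-related data lists "Sequential Organ Failure Assessment (SOFA) score at baseline" and APACHE II, called "a validated and commonly applied severity of disease classification system", as well as APACHE IV, SAPS II and lactate. It says that higher APACHE II and SAPS II scores go with a higher risk of death, and that SOFA is scored daily in the ICU. The Study procedures section mentions the scores again, but only as clinical data to extract. Nowhere are they named as adjustment variables.

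**The concern.** None of the four named covariates measures acute severity directly. The Background links raised I-FABP to intestinal ischemia and the systemic inflammatory response syndrome, so a correlation between the marker and severity at entry is plausible. Severity also drives death. A model without it can credit the marker with prognostic information that routine scores already give.

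For organ dysfunction the outcome is a rise in SOFA, and the natural covariate is the value from which the rise is counted. If patients who enter with high scores tend to fall back, a marker that tracks entry severity will be associated with fewer rises. That could hide a real effect.

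The Discussion wants the marker to support clinical measures before irreversible damage. It therefore matters whether it adds anything to what the unit already knows.

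**Working it through.** **Plan figures.** Measurements per patient: 72/6 + 1 = 13, as stated. The sample-size section's power figure concerns the IAH versus control comparison and is not affected. The article gives no figure for the prognostic model, so every input below other than n = 200 is an assumption.

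**Mortality.** Let S be standardised severity at entry, logit P(death) = −1.2 + b·S with b = ln 2.5 = 0.916 (about 26% deaths), and let the marker M have correlation r with S and no effect of its own. Given M, S has mean r·M and variance 1 − r². The log odds ratio of M without S is then approximately b·r / √(1 + 0.346·b²·(1 − r²)), where 0.346 is the usual logistic-normal constant and b² = 0.840.

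| r | b·r | divisor | OR by formula | OR simulated | significant |
|---|---|---|---|---|---|
| 0.2 | 0.183 | 1.131 | 1.18 | 1.17 | 17% |
| 0.3 | 0.275 | 1.124 | 1.28 | 1.27 | 31% |
| 0.4 | 0.367 | 1.115 | 1.39 | 1.39 | 51% |

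The simulation used 2000 replicates. With severity in the model the odds ratio was 1.00, significant in about 5%. A second set-up (entry SOFA mean 8, true SD 3, noise SD 1.5, log-odds of death 0.8 per 3 points, 600 replicates) gave about 1.28, 1.51 and 1.8 for r = 0.3, 0.5 and 0.7, significant in about 30%, 70% and 94%. The upward shift appeared in every scenario run.

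**SOFA increase.** Let z0 and z1 be entry and later SOFA in SD units, with correlation ρ and equal spread. Then z1 − z0 = (ρ − 1)·z0 + noise, and a marker that tracks only z0 has correlation −r·√((1 − ρ)/2) with the change. At r = 0.3 this is −0.15 for ρ = 0.5, −0.12 for ρ = 0.7 and −0.07 for ρ = 0.9. The distortion is driven by how far SOFA regresses to the mean. Simulated rejection rates for a null marker (rise of at least 2 points, 1000 replicates):

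| Entry to later SOFA | r = 0.2 | r = 0.3 | r = 0.4 |
|---|---|---|---|
| ρ = 0.5 | 18% | 36% | 55% |
| ρ = 0.7 | 11% | 21% | 31% |
| ρ = 0.9 | 6% | 8% | 10% |

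At ρ = 0.5 the odds ratios per SD were 0.86, 0.79 and 0.72. With slope 1.0, so no regression to the mean, they were 1.00 to 1.02, significant in 3% to 5%. With slope 1.3, where sicker patients deteriorate further, they were 1.18 to 1.35, the opposite direction. The second set-up, which adds measurement noise at entry, gave for r = 0.3, 0.5 and 0.7:

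- slope 0.7: 0.78, 0.66, 0.55
- slope 1.0: 0.89, 0.83, 0.76
- slope 1.3: 1.03 to 1.05

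With baseline SOFA in the model all of these returned to about 1.0.

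**Masking.** With a true conditional odds ratio of about 1.5 per SD and r = 0.2, power was 18% unadjusted against 66% adjusted at ρ = 0.5, and 48% against 83% at ρ = 0.7.

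**Does clustering help?** A patient random intercept is assumed independent of the marker, so it does not absorb severity, and mortality is constant within a patient. A random-intercept logistic model with three daily rows per patient, a time-varying null marker and ρ = 0.5 (200 replicates) gave odds ratios of 0.85, 0.77 and 0.70 for r = 0.2, 0.3 and 0.4, significant in 14%, 32% and 53%. With baseline SOFA they were 0.99 to 1.01, significant in 5% to 6%.

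**The case against.** The covariate list is illustrative, and this is a condensed article. A severity score is not named rather than ruled out, and an analysis plan that is not shown could add it. That stands, and it limits the point to naming the covariate. It does not remove the point, because the article does choose which covariates to name and omits the most obvious ones.

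The stated aim is to identify patients at risk, which is prediction. A marker that tracks severity does predict death, so its unadjusted odds ratio is a true association and the rejection rates above are not type I errors for that question. This also stands. They are errors only if the odds ratio is read as information beyond severity.

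A reader might infer that the marker will look protective for organ dysfunction. The documents do not support that. The direction depends on how SOFA evolves, and the distortion vanishes or reverses if sicker patients deteriorate further. The ceiling of SOFA adds almost nothing: at an assumed mean of 7 and SD of 3.5, removing the cap at 24 leaves the odds ratios essentially unchanged. The article also does not say from which value an increase is counted. With daily scoring, a day-to-day rise is possible, and entry SOFA would then not be the matching covariate.

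Nor is this the only analysis bearing on the aim. The same section plans, numbers permitting, univariate comparisons of patients with and without ACS and of those who died and survived. The prognostic model is the only adjusted one.

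Finally, the simulations used one or three rows per patient instead of up to 13, and none included the four named covariates. If those carry some severity, the distortion would be smaller.

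**Conclusion.** The point holds in limited form. The only adjusted prognostic analysis, run with the covariates it names, is poorly placed to separate the marker from severity at entry, although the data to do so are collected.

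For mortality the bias is upwards in every scenario tried. With r between 0.2 and 0.4 and a severity odds ratio of 2.5 per SD, a marker with no effect of its own is significant in about 17% to 51% of runs. For SOFA increase the figure runs from about 5% to 55% over the regressing scenarios and the case without regression. The shift is typically downwards under regression to the mean, but its sign and size are unknown.

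All of this rests on assumed correlations and simplified models. It shows what can happen, not what will. The change is worth making because it costs almost nothing.

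**What to change.** In the Statistical analysis section:

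- **Organ dysfunction:** name SOFA at T0 (enrolment), as a continuous covariate, and define the increase from that same value. Daily scoring makes it available for patients who enter later in their stay.
- **Mortality:** name one severity measure already collected, either SOFA at T0 or one admission score. SAPS II covers the first 24 hours of ICU admission, so an admission score may predate enrolment for late entrants. One is enough, since the scores overlap.
- **ACS:** do the same only if the number of events allows. Otherwise keep that model descriptive.
- **Reporting:** give the unadjusted and adjusted I-FABP odds ratios side by side, the first for plain prediction and the second for value beyond routine severity scores.

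The cost is a few sentences and one degree of freedom per model, with no new data. The Background places intestinal damage upstream of organ dysfunction, so entry SOFA may already contain part of the effect and the adjusted odds ratio may be attenuated. That is a further reason to show both.

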## Methods/Design

### Study design and setting

Multicenter prospective observational study of 200 patients admitted to the ICU of Erasmus MC, University Medical Center Rotterdam (Rotterdam, The Netherlands) or Radboud University Medical Center Nijmegen (Nijmegen, The Netherlands), who are at risk for developing IAH or ACS according to the definitions of the World Society of the Abdominal Compartment Syndrome [3]. Since it was suggested that patients who have undergone liver transplantation should also be screened for IAH [21,22], liver transplantation has been added to the list of risk factors. The study is registered at the Netherlands Trial Register (NTR4638).

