### Outcome measures

I-FABP levels will serve as primary outcome measure. Urinary and serum concentrations of I-FABP will be analyzed in duplicate using a highly specific, commercially available enzyme-linked immunosorbent assay (ELISA) that selectively detects human I-FABP (HyCult Biotechnology, Uden, The Netherlands). The ELISA will be performed following the supplier’s protocol. I-FABP levels in urine will be adjusted to urinary creatinine levels.

Claudin-3 levels will serve as secondary outcome measure. Urinary levels of Claudin-3 will be analyzed in duplicate either by ELISA (if available at time of analysis) or by Western blotting. Claudin-3 levels in urine will be adjusted to urinary creatinine levels. If analyzed from Western blots, equal amounts of each sample (adjusted to urinary creatinine levels) will be separated by sodium dodecyl sulphate polyacrylamide gel electrophoresis (SDS-PAGE), transferred to a polyvinylidene fluoride (PVDF) membrane and probed using primary antibody to Claudin-3 (Rabbit anti-claudin-3 (34–1700), Zymed Laboratories, San Francisco, CA). After incubation with goat anti rabbit HRP-conjugated secondary antibody (Jackson, West Grove, PA), a signal will be detected by supersignal west pico chemiluminescence substrate (Pierce, Etten-Leur, the Netherlands). Band intensities for each sample will be semi-quantitatively analyzed using Quantity One (Biorad, Hercules, CA). This is a straightforward approach for semi-quantitative assessment of protein levels. Urinary creatinine levels in the collected samples will be determined at the Clinical Chemistry department.

The occurrence of (increasing) organ dysfunction will be based upon the SOFA score.

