**ASSESSMENTS:**			
**Baseline variables**	X		
**Disease-related variables**	X		
**IAP measurement**		X	
**Blood sample**		X	
**Urine sample**		X	
**I-FABP measurement**		X	
**Claudin-3 measurement**		X	
**Creatinine measurement**		X	
**Treatment-related variables**		X	
**SOFA score**		X	
**Adverse events**		X	X
**Length of ICU stay**		X	X
**Mortality during ICU stay**		X	X
**Secondary interventions**		X	X

*Patients are considered eligible as soon as two IAH risk factors are present. This can either be at ICU admission or later on during ICU stay.

**Patients are followed until 72 hours or until discharge from the ICU, whichever comes first. Measurements are performed every six hours.

Urine samples for measurement of I-FABP, Claudin-3 and creatinine levels: A single fresh specimen of urine will be collected from the urinary bladder catheter that is already in situ. Samples will be kept on ice and then frozen at −80°C in aliquots within two hours of collection.Blood samples for measurement of serum I-FABP levels (NB: this only applies to patients enrolled at Erasmus MC, Rotterdam, the Netherlands): A single blood sample (10 mL) will be drawn from the arterial line that is already *in situ*. Blood will be collected in pre-chilled vacutainer containing EDTA as anticoagulent (BD Vacutainer, Becton Dickinson Diagnostics, Aalst, Belgium) and kept on ice. Blood will be centrifuged at 4°C, 4000× g for 15 minutes. Serum will be stored in aliquots at −80°C within 2 hours until analysis.

The reason for following up on patients during the first 72 hours after enrollment is based upon our observation (unpublished data) that over 95% of patients that deteriorate clinically due to increased IAP will do so during the 12–24 hours. In order not to miss any patients that may deteriorate somewhat later (*e.g.*, due to leak at the surgical site), we have set the time frame at 72 hours.

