### Statistical analysis

Data will be analyzed at the end of the study using the Statistical Package for the Social Sciences (SPSS) version 21 or higher (SPSS, Chicago, Ill., USA) and will be reported following the STrengthening the Reporting of OBservational studies in Epidemiology (STROBE) guidelines. No interim analysis will be done. Normality of continuous data will be assessed by the Shapiro Wilk tests and by inspecting the frequency distributions (histograms). Homogeneity of variances will be tested using the Levene’s test.

Descriptive analysis will be performed in order to report baseline characteristics (intrinsic variables and disease-related variables) and outcome measures of the entire cohort as well as for the group of patients that develop IAH (IAH group; IAP of 12 mmHg or higher on two separate recordings) versus those that do not (control group). For continuous data mean and SD (parametric data) or medians and percentiles (non-parametric data) will be calculated and reported. For categorical data, numbers and frequencies will be calculated and reported for the entire cohort and for the IAH and the control group separately.

Univariate analysis will be performed in order to test the difference in the primary and secondary outcome measures between the IAH group and the control group. Continuous data such as the I-FABP level (primary outcome) of the Claudin-3 level (secondary outcome) will be tested using a Student’s *T*-test (parametric data) or a Mann Whitney *U*-test (non-parametric data). Chi-squared analysis will be used for statistical testing of categorical data such as the number of secondary interventions. A p-value <0.05 will be taken as threshold of statistical significance. Depending upon the number of patients within the cohort of the study that develop ACS and the mortality rate, similar tests will be used to compare data for those who developed ACS (or those who died) versus those who did not. The patient cohort to be included will be heterogeneous by nature, as IAH and ACS risk factors will differ between patients. If it is possible to identify subgroups of patients (*e.g.*, liver transplant patients) subgroup analyses may be performed. P-values <0.05 will be taken as threshold of statistical significance.

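### The primary urinary I-FABP comparison pools two centres in an unadjusted test, so any centre difference in both IAH rate and I-FABP level would be counted as an IAH difference

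*Protocol article*

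**What the plan says.** All references are to the protocol article.

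- **Study design and setting:** 200 patients are recruited at two ICUs, Rotterdam and Nijmegen.
- **Outcome measures:** "I-FABP levels will serve as primary outcome measure". The main aim, at the end of the Background, concerns the urinary level; serum I-FABP is a secondary aim.
- **Statistical analysis, group comparison:** "Univariate analysis will be performed in order to test the difference in the primary and secondary outcome measures". Patients with IAH are set against controls, and the test is Student's t or Mann-Whitney U. No stratum or adjustment variable is given. The section acknowledges that risk factors will vary from patient to patient and allows subgroup analyses where subgroups can be identified.
- **Statistical analysis, prognostic model:** a generalised linear latent and mixed model has IAH, ACS, new organ dysfunction or mortality as the dependent variable and the biomarker as a time-dependent predictor. Patient is the clustering unit. The adjustment list opens with "Additional covariates such as age, gender" and also gives the count of risk factors and BM as examples. Centre is not among the examples.
- **Study procedures, sampling text under Table 1:** for serum I-FABP, "this only applies to patients enrolled at Erasmus MC, Rotterdam".
- **Sample size calculation:** 120 controls and 80 IAH patients, control mean 20.0 and SD 10.0 ng/mL, two-sided 5% level, power above 90% for a 0.5 SD increase.

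**The concern.** Patients enter the IAH group by what happens to them, not by allocation, so a variable related to both IAH status and I-FABP can produce a difference between the groups. Centre is an obvious candidate. Two university ICUs may admit different mixes of the listed risk conditions, may enrol at different points in the 48-hour window, and rely on their own staff for bladder pressure readings and urine handling. A two-sample test on the pooled data cannot separate such a difference from one that goes with IAH itself.

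The prognostic model does not repair this. It is a different analysis with the biomarker on the predictor side, and clustering on patient handles repeated samples, not systematic differences between centres. Without a centre term, the quantity at risk in that model is the biomarker-outcome odds ratio.

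**Working it through.** **Step 1: the plan's own figure.** Inputs from the Sample size calculation: 120 v 80, standardised difference 0.5, two-sided 5%.

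Effective size = 1/(1/120 + 1/80) = 48. Power = Φ(0.5 × √48 − 1.96) = Φ(3.464 − 1.96) = Φ(1.504) = 93.4% (93.2% by the noncentral t). The stated power above 90% reproduces for the unadjusted test.

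**Step 2: bias in the pooled difference.** The documents give no enrolment, IAH rate or I-FABP level by centre. Assumptions: 100 patients per centre, 80 IAH patients in total (the plan's number), within-centre SD 10 ng/mL (the plan's control SD), and no IAH difference within either centre. Centre A has the higher I-FABP, by g.

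Bias = g × [P(centre A | IAH) − P(centre A | control)]

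With IAH in 50 patients at A and 30 at B: 50/80 − 50/120 = 0.625 − 0.417 = 0.208. For g = 5 ng/mL the bias is 0.208 × 5 = 1.04 ng/mL.

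**Step 3: false-positive rate, same case.**

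- True standard error of the difference, given the split: 10/√48 = 1.443.
- The test's own standard error also absorbs the centre gap. Group variances are 100 + 25 × 0.625 × 0.375 = 105.9 (IAH) and 100 + 25 × 0.417 × 0.583 = 106.1 (control). The pooled SD is 10.30 and the standard error 10.30/√48 = 1.486.
- Critical difference: 1.96 × 1.486 = 2.91.
- Rejection probability: 1 − Φ((2.91 − 1.04)/1.443) + Φ((−2.91 − 1.04)/1.443) = 0.098 + 0.003 = 10.1%.

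**Step 4: range.** Each cell gives bias in ng/mL and false-positive rate. The last column is the power of a centre-stratified comparison for 5 ng/mL (0.5 SD).

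| IAH at A / B | g = 2.5 | g = 5 | g = 10 | Stratified power |
|---|---|---|---|---|
| 40 / 40 | 0; 4.8% | 0; 4.3% | 0; 2.8% | 93.4% |
| 45 / 35 | 0.26; 5.2% | 0.52; 5.7% | 1.04; 7.3% | 93.1% |
| 50 / 30 | 0.52; 6.3% | 1.04; 10.1% | 2.08; 23.0% | 92.4% |
| 60 / 20 | 1.04; 10.9% | 2.08; 28.6% | 4.17; 76.8% | 88.5% |

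With g = 0 the bias is zero and the rate 5% in every row.

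**Step 5: cost of stratifying.** The effective size becomes the sum over centres of (IAH × control)/100. At 50/30 it is 50 × 50/100 + 30 × 70/100 = 46, and power = Φ(0.5 × √46 − 1.96) = Φ(1.431) = 92.4%. At 60/20 it is 24 + 16 = 40, and power = Φ(1.202) = 88.5%.

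These are normal approximations for the t-test. The plan adjusts urinary I-FABP to creatinine, so the ng/mL values are best read in SD units: in the worked case, a 0.5 SD centre gap gives about 0.10 SD of bias.

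**The case against.** The strongest reply is that nothing in the article says the centres differ. The remark on heterogeneity concerns patients, not sites. Eligibility, pressure technique, urine handling and the ELISA are common to the study, and one researcher measures the biomarkers. Confounding needs a difference in both IAH rate and I-FABP, and the larger error rates need a centre gap of 10 ng/mL, as large as the planned rise from 20 to 30 ng/mL. The plan could also be read as asking only whether levels differ between the groups, in which case the within-centre null used above is not its hypothesis. All of this limits the size of the problem. It does not remove it: common procedures do not equalise case mix, and a difference that merely reflects which hospital a patient was in would not support the diagnostic aim.

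A reader might infer more than the text supports:

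- **That the prognostic model excludes centre.** The covariate list is introduced as examples. Centre is not named, but it is not ruled out either, and a full list may stand in a document not shown.
- **That a severity score should be added too.** This is debatable. IAH may already be present at enrolment, and the Background says that IAH itself causes organ dysfunction, so adjusting for SOFA or APACHE could remove part of the association under study.
- **That urine and serum results are confounded by centre.** No urine-versus-serum comparison is planned, and serum comes from one centre, so the serum comparison cannot be confounded by centre.
- **That the analysis must be on a log scale.** Nothing in this point requires it.

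**Conclusion.** The concern holds in a limited form. The primary urinary I-FABP comparison is fixed as an unadjusted test between non-randomised groups pooled over two centres, and a version that accounts for centre is better at little cost. This is a choice the article states, not a detail left to another document.

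The size is unknown. Under the assumptions above, the false-positive rate is about 10% for a 50/30 IAH split with a 5 ng/mL gap, stays between 5.2% and 7.3% at 45/35, and does not exceed 5% when IAH rates are equal. It would be wrong to conclude that the type I error of this study is inflated: that depends on two centre differences the documents neither show nor exclude. The effect on the odds ratios in the prognostic model was not quantified. No figure stated in the article changes.

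**What to change.** In Statistical analysis:

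1. Make the primary urinary I-FABP comparison a linear model on IAH group with centre as a fixed term or, if a non-parametric test is used, a test stratified by centre (for example van Elteren). With two centres, a fixed term or stratum is the suitable form.
2. Report the unadjusted t-test or Mann-Whitney result beside it.
3. Name centre as a fixed covariate in the prognostic mixed model.

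No new data are needed, since the recruiting hospital is known for every patient. The cost is a little power for a 0.5 SD difference: 93.4% falls to 92.4% at a 50/30 split (about 1 point) and to 88.5% at 60/20 (about 5 points, just under the stated 90%). If IAH rates are equal across centres, nothing is lost.
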